## Abstract

**Background:**

Coronavirus disease 2019 (COVID-19) is a novel global public health emergency. Prenatal care (PNC) providing institutes should identify the needs and demands of pregnant women by optimizing the means of PNC services during the COVID-19 pandemic. The present study aims to: a) explain prenatal care experiences; b) assess the factors affecting self-care, and c) present a prenatal care guideline and Strategies to improve the PNC.

**Methods:**

This mixed-methods study with a sequential explanatory design consists of three phases. The first phase is a qualitative study exploring the prenatal care experiences among pregnant women. In this phase, the subjects will be selected through purposive sampling; moreover, in-depth individual interviewing will be used for data collection. Finally, the conventional content analysis approach will be employed for data analysis. The second phase is quantitative and will be used as a cross-sectional approach for assessing the association between psychological factors of self-care. In this regard, a multistage cluster sampling method will be used to select 215 subjects who will be visited in health care centers of Tabriz, Iran. The third phase will be focusing on developing a prenatal care guideline and Strategies, using the qualitative and quantitative results of the previous phases, a review of the related literature, and the nominal group technique will be performed among experts.

**Discussion:**

The present research is the first study to investigate the prenatal care experiences and factors influencing self-care among pregnant women during COVID-19 pandemic. For the purposes of the study, a mixed-methods approach will be used which aims to develop strategies for improving health care services. It is hoped that the strategy proposed in the current study could lead to improvements in this regard.

**Ethical code:**

IR.TBZMED.REC.1399.003.

## Plain English summary

Coronavirus disease 2019 (COVID-19) is a global public health emergency and a novel, highly contagious pneumonia caused by the severe acute respiratory syndrome coronavirus 2 (SARS-CoV-2). Pregnant women are more susceptible to viral infection due to pregnancy alterations. Social distancing program and fear of getting the sick lead to the reduction of prenatal care referrals, additionally pregnant women are also more willing to reduce the frequency of prenatal care. The lack of PNC during pregnancy might be drastically harmful. Prenatal care services institutes should identify the fears and demands of pregnant women during the COVID-19 pandemic by optimizing the means of PNC services and providing a service for the safety and well-being of pregnant women. The current study provides precise information about the prenatal care experiences of pregnant women, and the factors influencing it. This study will be used in the mixed methods approach with the sequential explanatory design and is comprised of three phases. The first phase is qualitative and will be exploring the experiences of pregnant women. The second phase is quantitative and will be used as a cross-sectional approach to assess the factors affecting self-care in pregnant women in Tabriz. The findings of the qualitative and quantitative phases, the literature review, and the nominal group technique will be used to establish some strategies to improve and may promote prenatal care.

## Introduction

The COVID- 19 disease is an emerging infection and also a re-emerging viral respiratory disease that has affected most countries in the world and its prevalence is increasing [1–3]. The virus is rapidly spreading around the world and due to the rapid spread of the virus, the World Health Organization (WHO) has identified it as a contagious pandemic disease [4]. Despite the strong efforts taken to control the epidemic, Nearly 5 million people worldwide are reported to have contracted the infection [5, 6]. The current state of the COVID-19 outbreak in all over the world is concerning [7, 8]. People over the age of 60 and those with weakened immune systems are at higher risk for the disease [9], and because the immune system is partially suppressed during pregnancy; pregnant women are more vulnerable to viral infections and their complications; thus COVID-19 pandemic might have serious consequences for pregnant women [1, 10]. The available data about effects of COVID- 19 on pregnancy and its probable complications seems to be insufficient [9, 11]. However, due to the physiological changes in maternal immune and cardiopulmonary systems, pregnant women are more likely to develop severe illness after infection with respiratory viruses [2, 10]. In 2009, pregnant women accounted for 1% of patients infected with influenza A subtype H1N1 virus, but they accounted for 5% of all H1N1-related deaths [12]. Severe complications have also been reported in SARS and MERS viruses epidemic, including tracheal intubation, hospitalization in the intensive care unit, renal failure, and death during pregnancy [13]. Reviews of studies have shown that clinical signs, laboratory results, and radiographic criteria in pregnant women with COVID-19 are similar to other affected adults, but the risk of developing COVID-19 disease in pregnant women is high for the reasons stated above and there is the possibility of complications in pregnancy and newborn infection [14]. These factors have led to anxiety and stress in pregnant women and their families [1, 15]. On the other hand, with the rapid spread of the disease in different countries, including Iran, taking special precautions like physical distancing and quarantining are recommended to protect and prevent the disease [16]. However, social isolation and disconnection can cause sadness, concerns, fear, anger, irritation and frustration [17]. All of factors that mentioned above are effective in self-care and health-care behaviors [1]. Such behaviors are performed by individuals to maintain and promote health level and disease prevention [18]. However, pregnant women have concerns about how to take care of their pregnancies and how to carry out their plans for childbirth during the outbreak of the novel corona virus [1]. Social distancing program and fear of getting the sick lead to the reduction of prenatal care referrals, additionally pregnant women are also more willing to reduce the frequency of prenatal care visits [8, 19]. The lack of PNC during pregnancy might be drastically harmful [8]. According to the reports; most of them are interested in getting online access to health information and services [8, 15]. Since qualitative studies can be helpful for a deep understanding of a particular phenomenon, and also, due to insufficient studies regarding prenatal care and its barriers or facilitators during COVID– 19 pandemics, present study was designed to explore factors affecting prenatal care. So appropriate interventions and guidelines can be developed in this regard.

### Objectives

The objectives of each phase are as follows:

### Objectives of the first phase: qualitative study

To explore prenatal care experiences among pregnant women during the COVID-19 pandemic.To explore views about barriers and facilitators of prenatal care among pregnant women during the COVID-19 pandemic.

### Objectives of the second phase: quantitative study

To determine self-care behaviors among pregnant women during the COVID-19 pandemic.To determine fear of COVID-19 among pregnant women during the COVID-19 pandemic.To determine anxiety of COVID-19 among pregnant women during the COVID-19 pandemic.To determine perceived stress among pregnant women during the COVID-19 pandemic.To determine the association between fear of COVID-19 with self-care behaviors.To determine the association between anxiety of COVID-19 with self-care behaviors.To determine the association between perceived stress with self-care behaviors.

### Objectives of the third phase

To develop a prenatal care guideline and Strategies to improve the PNC and increase the self- care skills during the COVID-19 pandemic.

## Methods/design

### Study design

A mixed methods sequential explanatory design will be used to conduct this study by collecting, analyzing, and integrating the qualitative and quantitative data. The mixed-methods paradigm is based on the principles and logic of pragmatism. According to this paradigm, the mixed use of qualitative and quantitative approaches results in a better understanding of the problem [20]. This study will have three phases, and the qualitative and quantitative data will be collected in the first and second phases, respectively. Phase one is an exploratory qualitative study, which aims to explore prenatal care experiences among pregnant women during the COVID-19 pandemic. Phase two is a cross-sectional study, which aims to assess the factors affecting the self-care behaviors among pregnant women during the COVID-19 pandemic. Phase three is about developing an evidence based and a culturally sensitive guideline based on literature review, the results of phase one and two and experts’ opinion using the nominal group technique (Fig. 1).

**Fig. 1 Fig1:**
[figure not shown]
Study diagram

### First phase: qualitative study

The first Phase is an exploratory qualitative study with a conventional content analysis approach to explore the prenatal care experiences and views about barriers and facilitators of prenatal care among pregnant women during the COVID-19 pandemic.

### Sampling method

The research participants will be selected through purposive sampling among pregnant women. Inclusion criteria included: having Iranian nationality and residency in Tabriz, ability to understand and to convey concepts to the researcher, single pregnancy with the age range of 18–40 years, pregnancy over 10 weeks, having the tendency and ability to express and transfer concepts, considering the maximum variability in terms of factors such as education, age, socioeconomic status, having any disease or medical, obstetric risk factor identified on the basis of the family’s health records or, as the pregnant woman claims, also requiring special care or relative or absolute rest for the mother, as well as the withdrawal and non-attendance of the pregnant women were considered as the exclusion criteria.

### Data collection

Qualitative data will be collected using in-depth and semi-structured interviews, containing open questions. Before conducting the interviews, the research team reviews the questions, and the ways to obtain valid data, then focuses on research questions. The interviewer will pilot the interview on with a subset of participants, and will use this information to further refine the guide with respect to culturally sensitive and appropriate questions. The interview will begin with a key question, “What were your experiences and feelings about prenatal care during the covid-19 pandemic?”, “Do you think the covid-19 pandemic has affected your prenatal care?”. Then, the interview will continue by presenting other questions, such as “How do you cope with the difficulties of prenatal care during the covid-19 pandemic?”, “What can you do to prevent the disease during pregnancy?”, “What do you think about prenatal care support?”, “Have you received support?”, “In your opinion What factors can be helpful in prenatal care?”, and “What factors do you think may hinder your prenatal care?”. The interview will continue with more in-depth items, such as “what do you mean? Why? Can you explain further? Can you give an example?” to explore the depth of their experience. During the interview, as far as possible, the Note field will be used and non-verbal data such as tone of voice and behaviors will be recorded, too. The sampling will continue until data are saturated. All interviews will be carried out in care centers in a quiet room and without someone other than the interviewees.

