### Sample size and sampling method

Considering an acceptable error of 0.1 around the mean (m = 2.14), 95% confidence coefficient, 90% statistical power, and the standard deviation of 1.11 related to fear of COVID- 19 [21], the necessary sample size was determined to be 103 pregnant women, and regarding 95% confidence coefficient, 90% statistical power, an acceptable error of 0.05 around the mean (m = 71.9), and the standard deviation of 11.48 related to self-care, also an acceptable error of 0.05 around the mean (m = 60.27), and the standard deviation of 13.12 related perceived stress [18], the necessary sample size was determined to be 40 and 73 pregnant women, respectively. Also, Considering 57% anxiety with an acceptable error of 0.1 [22], the necessary sample size was determined to be 130. As the sample size based on anxiety was greater, this was the sample size sought. Regarding cluster sampling and design effect of 1.5, the final sample size was considered to be 215 pregnant women.
$$ n=\frac{{\left({Z}_{1-\frac{a}{2}}\right)}^2x\;p\left(1-p\right)}{d^2} $$

Sampling will be conducted in the healthcare centers in Tabriz. There are 82 public healthcare centers (*n* = 40) and posts (*n* = 42) in different regions of the city that provide primary care services, free of charge. Most of the pregnant women have health records in these healthcare centers and posts. A two-stage cluster sampling will be carried out so that 13 healthcare centers and 14 healthcare posts were selected using a randomizer software (www.random.org). A list of all pregnant women at each center will be extracted from the health records and the samples will be randomly selected from the ordered numbers. Afterward, using the phone number registered in each record, the researcher will call the potential participants and will invite them to participate in the study and will visit them in their homes if needed. Eligible participants will be provided with full explanations about the study objectives and procedures. Also, informed consent will be obtained before collecting information, and the importance of honest answers to the questionnaire will be emphasized, and they are asked to complete the anonymous questionnaires in a private room. A number of participants are likely to be illiterate, so the questionnaires will be completed by the researcher in order that the data collection method to be the same for all individuals.

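### Phase 1 explores barriers to prenatal care but holds every interview in a care centre, so women who avoid or cut centre visits are likely to be under-represented

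*Protocol article*

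**What the plan says.** The second objective of the first phase reads: "To explore views about barriers and facilitators of prenatal care among pregnant women during the COVID-19 pandemic". The Introduction explains why attendance is part of the problem: "Social distancing program and fear of getting the sick lead to the reduction of prenatal care referrals". It adds that women themselves are more inclined to cut down on visits, and the Discussion repeats that fear lowers attendance.

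Under Sampling method (first phase), recruitment is described broadly: "The research participants will be selected through purposive sampling among pregnant women". Maximum variation is sought on education, age and socioeconomic status, given as examples. Use of prenatal care is not named. The same sentence ends: "as well as the withdrawal and non-attendance of the pregnant women were considered as the exclusion criteria". What is not attended is left unsaid.

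Under Data collection (first phase), the setting is fixed: "All interviews will be carried out in care centers in a quiet room", with nobody else present. No home, telephone or online alternative is mentioned. Sampling stops at data saturation, and no number of interviews is given.

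In the second phase, women are drawn from health records and telephoned, and the researcher "will visit them in their homes if needed".

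**The concern.** Whether a woman can take part depends on something close to what is being studied. To describe what keeps her from a care centre, she must first come to one. Those most deterred by fear of infection are the least likely to accept that condition, and their accounts bear most directly on the barriers objective.

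The stopping rule does not protect against this. Saturation is judged on the interviews obtained, so new themes can dry up among women willing to come to a centre while the barriers of those who stay away have not been heard.

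What is at stake is completeness and transferability. The guideline phase takes the qualitative results to 10–12 experts. A group of barriers missed in the interviews would reach them only through other inputs, none of which is described as asking women in Tabriz openly what hinders their care.

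**Working it through.** No arithmetic applies. The first phase is qualitative and states no sample size, precision or power, and the sample-size figures of the second phase have no bearing on this point. The check sets the sections side by side.

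1. **Objective against premise.** The objective is to learn about barriers to prenatal care. The Introduction names fear and distancing as reasons for reduced use of that care. Avoiding or cutting visits is therefore part of the phenomenon under study.

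2. **Premise against venue.** The venue rule covers all interviews and places them in the kind of setting that the Introduction says women are avoiding. This is a stated rule and not a detail left out of a condensed article. Followed as written, it makes participation harder for avoiders than for attenders.

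3. **Is there an offset in the sampling?** Recruitment is among pregnant women generally, so current attendance is not required. But nothing directs recruitment towards women with missed or reduced visits: the named variation factors do not include use of care.

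4. **Is there an offset in the quality checks?** The Validation section lists review by participants, comments from colleagues and outside observers of the coding. These test how the collected interviews are read. They cannot supply interviews that were not held.

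5. **Is there an offset in the second phase?** Its reach is wider, through records, telephone calls and home visits if needed, and it records the number of prenatal care visits. Its instruments are a sociodemographic form and scales for fear, anxiety, perceived stress and self-care. No open question on barriers is described. It can show who attends less, but not in their own words why.

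6. **The non-attendance wording.** Two readings are possible.
   - *Missing the interview.* The pairing with withdrawal points this way. So do the second phase's exclusion criteria, which concern only incomplete questionnaires and unwillingness to continue. On this reading the criterion adds no selection of its own, although a woman who will not come to a centre for the interview would still be lost through the venue rule.
   - *Missing prenatal care.* This would exclude the most informative group, but the text does not establish it.

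7. **Size.** The documents give no proportion of women who avoid centres, no proportion of avoiders who would still agree to an interview there, and no Phase 1 sample size. Neither the extent of under-representation nor its effect on the themes can be computed.

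**The case against.** The strongest reply is that a venue is not a recruitment rule. Nothing bars a woman with missed visits from being invited, and the Introduction speaks mainly of fewer visits, not of none. Such a woman may well come once for an interview, and the interview guide asks directly whether the pandemic affected her care and what may hinder it. This stands. A reader might infer that avoiders are shut out altogether, or that almost none could enter the phase. That would require a woman who skips prenatal visits never to enter a centre for any purpose, and no section says so.

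A reader might also take non-attendance as a definite exclusion of women who miss prenatal care. The wording is ambiguous, and missing the interview is the likelier meaning.

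Nor do the documents support saying that the barriers found will be biased. A purposive qualitative sample does not estimate how common a barrier is, and what attenders report is not made wrong by what others were not asked. The risk is incompleteness.

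It would also be wrong to say that the guideline rests only on women who already reach care: it draws as well on the second phase, a literature review and expert opinion through the nominal group technique.

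Two further points carry some weight. The variation list is open, so use of care could be added in practice. And a quiet room in a centre is a defensible setting for an in-depth interview held in private with non-verbal behaviour recorded; home visits to complete questionnaires do not prove that home interviews are equally easy. These points lower the severity. They do not explain why the centre must be the only setting, or why the factor closest to the question is not named.

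**Conclusion.** The point holds as a cheap improvement. The plan requires centre-based interviews in the phase meant to find barriers, while its own premise is that women are reducing centre visits, and it names no sampling factor to counter this. Women who avoid or cut visits are likely to be under-represented, barriers particular to them may be missed, and saturation may be reached mainly among attenders.

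This rests on the Introduction's statement that fear and distancing reduce attendance, and on the assumption that women deterred from prenatal visits are also, on average, less willing to come to a centre for an interview. The size is unknown and cannot be derived from the document. No stated figure in the protocol is affected.

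**What to change.** Three changes of wording, best made before recruitment starts:

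- **Data collection (first phase).** Keep the care centre as one setting, but allow an interview at home, or by telephone or video, when a woman prefers not to come. Keep the requirement that nobody else is present, and record the setting or mode of each interview.
- **Sampling method (first phase), variation factors.** Add use of prenatal care, as regular versus missed or reduced visits, so that some women with missed or reduced visits are purposively recruited.
- **Sampling method (first phase), exclusion criteria.** State that non-attendance means not keeping the interview appointment.

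The cost is some travel time for home interviews and some loss of non-verbal data in remote ones. Home visits are already foreseen in the second phase. If the centre-only rule is kept, the limitation should be stated and carried into the material given to the expert group.

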### Data analysis

Data analysis process will be conducted simultaneously with data collection using MAXQDA software version 10. Qualitative data analysis can be conducted through qualitative content analysis based on the Graneheim and Lundman method [20]. In this approach, the data will be analyzed through repeated Reading strategy to obtain a full understanding of it. Then, the texts will be read word by word to extract the codes. First, the objective words that contain the key concepts will be specified. The researcher continued digging the text by taking notes from the initial analysis until the major codes will be extracted. In this process, the code labels reflecting more than one key thought will be directly extracted and specified. Then, the codes will be categorized based on their difference and/or relationships. The codes will be categorized into themes and main categories. Subcategories will be extracted based on differences and similarities.

### Validation

To validate the results, at first efforts will be made to build a friendly relationship with the participants. In order to increase the accuracy of the data and to verify accuracy of the data, after the registration, the interviews will be given to the participants to review and confirm their stated content and, necessary points will be any other content, it will be added to the data. Interviews will frequently be read by the corresponding author of the paper; then, the text of the interviews with the extracted codes and categories will be shared with the colleagues and their comments will be used. External monitoring will be also used to increase the reliability. Through providing the initial code derived from the analysis and examples of the extraction, as external observers, the concepts will be given to other researchers; who are not related to the study in order to determine whether they also will have a similar perception of the data or not.

